#### 2.4.2. Qualitative Analysis

The semi-structured interviews and focus group discussions were recorded and transcribed. These transcriptions, the interview notes, logs, Jump-in scans will be analysed using MAXQDA 2018. We will conduct a content analysis in which we use the framework of Fleuren et al. [29] (Figure 2). The analysis will be an iterative process and will be conducted by two independent researchers ([name] and [name], [name], [name] or [name], see Acknowledgements). At first, the researchers will do the analysis independently for all interviews at two schools. Then, the codes will be compared, and consensus will be reached, and one of the researchers then will code all the interviews.

## 3. Discussion

The purpose of this paper is to describe the mixed methods Extended Selection Cohorts design for the evaluation of an intervention targeting dietary habits, the methodical challenges due to the real-life setting and proposed solutions. This design enables us to collect valuable data on (1) the effects of a widely-disseminated intervention with a reach of over 22,000 children [17], (2) outcomes of children’s dietary behaviour reported by both parents and children (3) children’s dietary behaviour using self-reported (i.e., questionnaire) and objective measurements (i.e., photographs) and (4) the context, which helps interpretation of the outcomes. We chose this evaluation design because recruitment of comparable control schools and randomization was impossible. Due to the large-scale implementation of Jump-in in Amsterdam, finding a control group was virtually impossible. Furthermore, primary schools that enrolled in the Jump-in programme were predetermined. This prohibited random assignment to either an intervention or control group. We tackle this challenge by applying the quasi-experimental Extended Selection Cohorts design.

The ESC design is suitable in real-life settings in which the recruitment of control groups fails or intervention groups are predetermined, as it still allows comparison of same-age treatment groups [26]. Whereas in a standard Randomized Controlled Trial design, the intervention is randomly allocated to different schools; in the ESC design intervention and control groups belong to the same schools, and hence, fewer schools are needed. Since intervention and control groups belong to the same units and cohorts are represented by different grades, groups are recruited from a relatively stable population [26]. In many quasi-experimental designs treatment and control groups differ in socio-demographic characteristics which may be hard to monitor [26]. However, since in the ESC design groups originate from the same schools, groups are comparable in baseline characteristics (e.g., in age, SES and ethnicity). This is important in our setting, because dietary behaviour is likely different between different SES and ethnicity groups [4,45].

A limitation of the ESC design is the difference in the time points of data collection of control and intervention groups, since baseline measurements represent the control and the follow-up measurements represent the intervention groups. Therefore, the design does not allow to control for general societal time trends that coincide with the intervention, such as a new supermarket next to the school. To mitigate this limitation, we conduct an extensive process evaluation.

This evaluation study is set up in a complex real-life setting, which may influence how the intervention is delivered [27]. Contextual factors to consider are: the wide dissemination among primary schools in Amsterdam, the support of a team of health promotion professionals, and the embedding in health promotion programmes and Amsterdam’s municipality (i.e., ensuring structural, financial and political support and connections with other health promotion interventions in Amsterdam) [17]. These factors might influence the implementation and, thereby, the outcomes.

To get a grip on the complexity of the setting, we include a process evaluation. Process measures can be used to explain differences in effectiveness between clusters (e.g., schools), and understand how and under which conditions an intervention is effective [27,28].

Accurate measurement of dietary behaviour, especially in children, is challenging. In general, the validity of self-report is questionable, because children have a short attention span [35] and outcomes can be biased due to recall and social desirability [46,47,48,49]. For instance, children tend to overestimate their fruit and vegetable intake in self-reported dietary methods [50,51].

Another common challenge is to motivate people to participate and repeatedly fill out long questionnaires. In our study, data collection relied on a number of stakeholders to motivate children and parents to participate; we needed the help of the health promotion professional to contact primary schools, the school principal and Jump-in coordinator to approve study participation; lastly, the teachers to motivate children and parents to fill in questionnaires and allow us to photograph the food and drinks that children bring to school. Even though we incorporated strategies to optimise participation in this study (e.g., tailoring recruitment procedures to the schools’ needs), this remains challenging.

To address both these issues, we included photographs of children’s at-school food and drinks. This method is not prone to self-reported recall bias, and—compared to questionnaires—is less time consuming, labour intensive and costly. However, it can be questioned whether it is prone to social desirability, e.g., when children hide unhealthy foods or drinks during data collection, or are not honest about the content of covered products (i.e., due to hygiene reasons we did not unfold products wrapped in tinfoil).

Furthermore, this method measures the products children bring to school without knowing whether they actually consume it. Photographs might not be suitable to accurately assess quantity. However, in the present study, we were specifically interested in whether the intervention enabled a shift towards healthier alternatives (e.g., a shift from sugar-sweetened beverages to water). For this objective, photographs can be useful.

Although not extensively researched yet, some authors found that digital imaging is a reliable alternative method for measuring fruit and vegetable intake during school lunch [52]. The use of both questionnaires and photographs to measure dietary intake in our research allows us to assess the effect of the intervention and compare both methods.

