Box 1What is the Jump-in intervention?*Multi-component intervention*. Jump-in is a multi-component primary school-based intervention that aims to stimulate physical activity [18,20,21], active school recess play [22] and healthy dietary habits in primary school children in Amsterdam, The Netherlands. Jump-in mainly focusses on Amsterdam’s areas where health inequalities prevail and where obesity rates are highest, which often coincides with a target population with a relatively high percentage of children with a low socio-economic position and/or from ethnic minority groups. In order to stimulate healthy dietary habits, a school-wide healthy school nutrition policy is implemented at primary schools, which means that for the morning break children exclusively drink water, tea without sugar or milk (1), and eat fruit and vegetables (2); for lunch children drink water, tea without sugar or milk (3), and eat whole wheat bread or products (4); and special treats (e.g., during birthday celebrations) comprise of small portion sizes, healthy foods or are non-food treats (5).*Implementation strategies*. Jump-in comprises of a 3-year implementation process at schools, which is facilitated by a team of specialised health promotion professionals. After enrolment, the health promotion professional organises meetings with the school principal and the school’s Jump-in coordinator. The latter is a school employee who coordinates the implementation of the healthy nutrition policy and other parts of Jump-in. Together they formulate a tailored plan to fit the needs of the school, e.g., tailoring communication to different literacy levels and/or cultural backgrounds of children and parents who attend the school. The health promotion professional keeps structured and detailed logs of these meetings and implementation processes in a so-called Jump-in scan. Parental involvement is also an important aspect, because parents generally pack children’s lunchboxes and play an important role in children’s dietary habits at home. In order to stimulate teachers, parents and children to adhere to these outcomes, trained professionals such as dieticians provide workshops about corresponding themes (i.e., water, fruits and vegetables, breakfast and lunch, and treats). These professionals are trained to work with Jump-in’s target population. Posters and other communication and educational tools are provided to aid the embedding of the healthy nutrition policy in Jump-in schools. All programme components have been developed following the Intervention Mapping Protocol.*Embedding in municipal policy*. The Jump-in programme is structurally embedded within the Amsterdam Healthy Weight Approach (AHWA): an integral preventive programme to reduce and prevent obesity in Amsterdam [17,23]. This programme aims to achieve a healthier weight for more children in Amsterdam by addressing multiple settings (e.g., schools, neighbourhoods, health care, etc.) and stakeholders (e.g., professionals, parents, etc.) involved with children in Amsterdam [23]. AHWA was recently recognized by the WHO as a good practice example of how health behaviour change can be structurally shaped involving the target group in an urban setting [24].

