#### 2.1.2. Effect Evaluation

The Extended Selection Cohorts (ESC) design entails a cohort-longitudinal design with adjacent cohorts [25], that are measured at two or more time points [26]. Each cohort represents an age cohort including subjects of approximately the same age.

In our study, each cohort—represented by school grades—was measured three times: at baseline, 12 and 24 months after baseline measurements. Each cohort at follow-up was compared to the same-age adjacent baseline cohort group (see Figure 1). For instance, the measures of 2-year exposed cohort 3 (grade 5 in 2018–2019) were compared to the measures of 1-year exposed cohort 4 (grade 5 in 2017–2018) and to baseline measurements of cohort 5 (grade 5 in 2016–2017).

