*Document analysis*. Document analysis was included to assess process indicators, contextual factors and satisfaction. These documents comprised of Jump-in scan logs of effect data collection and interview notes. Jump-in scans are structured, uniform logs kept by the health promotion professionals to keep track of when which intervention components are implemented. It serves as an instrument to structure and aid the quality of intervention delivery and implementation. Furthermore, the logs of the effect evaluation data collection allowed us to monitor potential effect evaluation measurement flaws.

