### 2.4. Analyses

#### 2.4.1. Quantitative Analysis

Prior to data collection, we estimated that 107 subjects for each cohort was needed (d = 0.5, SD = 1.0, α = 0.05, power 80%) in order to detect a statistical difference between our control (i.e., T_0_) and intervention groups (i.e., T_1_ and T_2_). Assuming each class consisted of a minimum of 25 students, five schools were required. When we took into account the cluster design and possible non-response, we took a sample that consisted of twice the number of schools needed [44]; hence, the sample size was ten primary schools.

We will conduct a series of multilevel regression analyses. This analysis takes into account different clusters (i.e., class level, potentially school level). Same-age data from different time points and cohorts will be compared, in which cohorts consist of a group of children from the same age from all ten participating schools. We will create a variable for at-school consumption by combining the food and drinks consumed in the first and second school break, i.e., sugar-sweetened beverages, water or tea without sugar, milk, whole wheat bread, fruit, vegetables, snacks consumed at school. This will be done based on the parent and child questionnaires, and the photographs. Behavioural determinants (attitude, knowledge, social norm, modelling, physical environment, liking and habit formation) will be derived from the parent and child questionnaires.

To analyse the effect of the intervention on the combined scores of at-school dietary behaviour and behavioural determinants, we will use multilevel regression analyses. For continuous outcome variables we will use linear multilevel regression models with time point as first level variable and grade as second level variable. When variables are not normally distributed, we will use Poisson multilevel analysis. For categorical variables we will use logistic multilevel models. To examine whether observations cluster at school level, we will add schools as third level in the linear models. If this is the case, schools will be added to all models—creating a three-level structure—and for categorical variables we will shift to a GEE analysis.

To explore the moderation effects by SEP, age in years, sex and ethnicity, we will add interaction terms to the model. When these terms are significant, we will stratify the analyses for these specific subgroups.

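### The before–after contrast names no confounder covariates and rests on an asserted comparability that need not hold for responders; with calendar time also uncontrolled, it should be adjusted and worded as change since enrolment

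*Protocol article*

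**What the plan says.** - **Comparison.** Section 2.1.2: "Each cohort at follow-up was compared to the same-age adjacent baseline cohort group". The Discussion puts it as: "baseline measurements represent the control and the follow-up measurements represent the intervention groups".
- **Model.** Section 2.4.1 specifies, for continuous outcomes, "linear multilevel regression models with time point as first level variable and grade as second level variable", with school as a third level if clustering is found. Poisson, logistic or GEE versions serve the other outcome types.
- **Role of personal characteristics.** The same section: "To explore the moderation effects by SEP, age in years, sex and ethnicity, we will add interaction terms to the model". Stratified analyses follow if an interaction is significant. The only adjustment named is for diet at home, and its purpose is to study compensation.
- **Comparability.** Discussion: "since in the ESC design groups originate from the same schools, groups are comparable in baseline characteristics", with age, SES and ethnicity as the examples. The article adds that this matters because diet probably varies with SES and ethnicity.
- **Time trends.** The Discussion states that general societal trends cannot be controlled, then: "To mitigate this limitation, we conduct an extensive process evaluation".
- **Concurrent activity.** Box 1 places Jump-in inside a city programme that works "by addressing multiple settings (e.g., schools, neighbourhoods, health care, etc.) and stakeholders".
- **Implementation data.** Section 2.3.2 describes the Jump-in scans as "structured, uniform logs kept by the health promotion professionals to keep track of when which intervention components are implemented". Section 2.4.2 sends them to content analysis.

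**The concern.** The groups are not randomised and are measured in different school years. Grade and school are matched by design; year and response are not. Two kinds of difference can therefore enter the T1/T2 versus T0 contrast without being a Jump-in effect.

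1. **Who responds.** Shared schools make the enrolled pupils similar from year to year. They do not ensure that the families returning questionnaires are similar. If the SEP or ethnic mix of responders shifts between waves, and diet differs by SEP or ethnicity as the article expects, the shift appears as change in diet. An interaction term tests whether the effect differs between subgroups; listing a variable as a moderator does not commit the main estimate to adjustment for it.
2. **Calendar time.** Exposure and year coincide, so any common trend in school food passes straight into the estimate. The named response is a process evaluation, which supplies context and not a correction.

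At stake is whether the reported figure can be read as an effect of Jump-in or only as change since the schools enrolled.

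**Working it through.** The article gives no size for a trend or a responder shift, so there is no figure of its own to reproduce. The check is a comparison of statements, followed by an illustration on assumed inputs.

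**Step 1: which groups are compared.** In the article's own example, grade 5 in 2018–2019 (cohort 3) is set against grade 5 in 2016–2017 (cohort 5). These are essentially different children. Pooled over grades, the waves overlap. Child questionnaires cover grades 5–8, so grades 7–8 at T2 were grades 5–6 at T0: two of four grades. At T1 it is three of four. Turnover of pupils alone is therefore unlikely to produce a large shift; differential response would have to carry most of it.

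**Step 2: where response can differ.** Consent for the effect evaluation was opt-out (Section 2.2.2), and photographs were taken at school in all grades (Section 2.3.1). Parent questionnaires went home in an envelope and came back through the school. The Discussion calls motivating people to complete questionnaires repeatedly a challenge. The exposure to responder shift is thus greatest for parent questionnaires and least for photographs.

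**Step 3: size of a composition bias.** All inputs except the 250 are assumptions:
- prevalence 40%, so p(1−p) = 0.4 × 0.6 = 0.24
- design effect 2.2
- prevalence differs by 20 points between SEP groups
- low-SEP share among responders shifts by 10 to 20 points between waves
- n = 1500 per wave if grades are pooled, or n = 10 schools × 25 = 250 per grade, from the class size in Section 2.4.1

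Bias = share shift × prevalence difference = 0.10 × 0.20 to 0.20 × 0.20 = 0.02 to 0.04.

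SE = √(2 × 0.24 × 2.2 / n), treating the two waves as independent.

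| n per wave | SE | Bias / SE | False-positive rate, no true effect |
|---|---|---|---|
| 1500 (pooled) | √(1.056/1500) = 0.0265 | 0.75 to 1.5 | 12% to 33% |
| 250 (one grade) | √(1.056/250) = 0.065 | 0.31 to 0.62 | 6% to 9% |

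The last column is Φ(b/SE − 1.96) + Φ(−b/SE − 1.96), against a nominal 5%. The bias does not shrink with n, so pooling makes it weigh more.

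**Step 4: size of a calendar bias.** A common trend enters one-for-one. An assumed fall of 5 points a year in children bringing sugar-sweetened drinks would show as 2 × 5 = 10 points at T2. In SD units, with no true effect and SE = √(2 × DEFF / 250), an assumed drift of 0.1 SD is declared significant in 20% of cases and 0.2 SD in 61% (DEFF 1). With DEFF 2.2 the figures are 12% and 33%.

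**Step 5: can the process evaluation correct this?** Interviews were planned around T1, with T2 for schools that missed it (Section 2.3.2). Transcripts, notes, logs and scans go to content analysis (Section 2.4.2). Section 2.4.1 carries no process variable into the effect model. The process evaluation can therefore suggest whether a trend is plausible but cannot subtract it.

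**The case against.** Several points on the other side stand.

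- **The time-trend limitation is disclosed.** The article says openly that trends are not controlled and why control schools could not be found. Nothing is hidden. What remains is narrower: the word 'mitigate' promises more than a process evaluation can deliver.
- **A reader might infer that the plan declares an unadjusted analysis.** It does not. Section 2.4.1 gives levels and moderators and no covariate list, and a fuller analysis plan might contain one. Grade matching and clustering are also handled. What keeps the point alive is that the article goes beyond silence: it assigns SEP, sex and ethnicity a role and gives a positive argument for why the groups are already balanced.
- **A reader might infer that a known city-wide trend biases the result.** Box 1 shows a concurrent programme of which Jump-in is part. It gives no trend in diet and no timing of neighbourhood or health-care activity around these schools. A possible confounder is documented, not a known one. The article also took steps against co-intervention: one school was excluded for joining comparable programmes (Section 2.2.1), and fruit days were avoided (Section 2.3.1).
- **A reader might infer that the scans could separate Jump-in from the trend.** All ten schools come from the 2016–2017 enrolment, and T0 serves as the control measurement in each. An indicator of components in force would be nearly aligned with wave, and the remaining variation may reflect school motivation.
- **Adjustment can introduce selection.** Socio-demographic data come from questionnaires. In grades 1–4 children fill in none, so the covariates depend on parents responding.

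**Conclusion.** The point holds in a limited form. The main contrast is non-randomised, and the stated models name SEP, sex and ethnicity only as moderators. The comparability argument covers enrolled pupils and leaves responders open, while the article itself regards SES and ethnicity as related to diet and participation as difficult. This matters most for the questionnaire outcomes and less for the photographs.

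No magnitude can be taken from the document. If prevalence is 40%, the design effect 2.2, the SEP gap 20 points and the responder shift 10 to 20 points, the composition bias is 2 to 4 points: about 0.8 to 1.5 SE with 1500 per wave and 0.3 to 0.6 SE at about 250 per grade. The calendar bias has no bound from the data described.

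Adjustment would address measured differences in case mix only. It would not address calendar trend, which is a matter of wording and attribution. The weakness limits what can be claimed and does not invalidate the study.

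**What to change.** 1. **Section 2.4.1.** Include sex, SEP and ethnicity as covariates in the main models where available. Keep grade as the age variable, since age was removed from the questionnaires from May 2018 (Section 2.2.2). The moderation analyses can stay as planned.
2. **Reporting.** Show responder characteristics at T0, T1 and T2 for each data source, with crude and adjusted estimates side by side.
3. **Discussion, time trends.** Replace the claim of mitigation with a statement that the process evaluation informs interpretation but does not remove a trend from the estimate.
4. **Wording of the main result.** Describe the contrast as change since enrolment, not as an effect attributable to Jump-in alone.

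A model using implementation timing from the Jump-in scans is at most optional and exploratory, and should be reported as not estimable if the schools implemented together.

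**Cost.** The variables are already collected, so this is analysis and text only. Records with missing SEP or ethnicity drop out of the adjusted models, mainly in grades 1–4, and that loss may itself be selective. The crude full-sample result should therefore stay visible next to the adjusted one.

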## 4. Conclusions

We aimed to provide an example of using a mixed-methods, quasi-experimental Extended Selection Cohorts design to evaluate the effectiveness of a school-based intervention on children’s dietary habits as well as the implementation process in real-life.

